## Methods/design

### Design and sample size

This protocol is for a study of two superiority RCTs with participant preference between the two interventions with 1:1 allocation to either intervention or wait-list within the preferred choice. The randomisation procedure will be web-based and automated; the allocation sequence will be generated and participants randomised using block randomisation by Qualtrics (www.qualtrics.com), the online survey software. Members of the research team involved in the day-to-day management of the study will be blind to block size. Assessments will be completed online by participants at baseline and post-intervention, independent from members of the research team, to reduce risk of bias associated with researcher-administered assessments.

Sample size calculations were conducted using G*Power [13]. The study aims to have 140 participants giving complete data sets at baseline and post-intervention within each part of the study (i.e. aiming for 140 MBCT-L and 140 CBT study completers). Given the pressures on staff time and the online data collection method, it is conservatively assumed that 40% of participants will fail to complete measures post-intervention. This means that we aim to recruit 234 participants into each part of the study.

Sample size calculations are based on an estimated medium between-group effect on post-intervention stress outcomes (Cohen’s *d* = .50) between the intervention and wait-list arms with 90% power and *p* = .05. For MBCT-L, the estimated medium effect size is based on between-group post-intervention effects on stress reported in previous trials of MBIs for healthcare staff [9, 12, 14]. For the CBT stress-management workshop it was not possible to estimate the effect directly based on published trials as previous research has evaluated CBT stress-management interventions running over several sessions. We therefore assume that the effect size will be smaller in the current study than the large effect reported in a meta-analysis of multiple-session CBT stress-management interventions in the workplace [34] and therefore estimate a medium effect size.

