### Planned data analysis

The intention in providing two interventions is to increase choice and accessibility. The intention is not to compare the effectiveness of the CBT intervention directly with the MBCT-L intervention and any such comparison would be problematic given the potential for selection bias (i.e. participants preferring MBCT-L may differ in a number of ways from participants preferring the CBT workshop). Intervention preference will be reported as the number and percentage of participants choosing each intervention type; however we would urge caution when interpreting these data as participant preferences may be driven by practicalities (e.g. location and dates of available courses) as much as by intervention preference.

Between-group differences at baseline on key demographic variables (age, gender, ethnicity, NHS trust, pay band and years working in the trust) and all outcome measures will be reported for each study. Findings will be reported for both intention-to-treat and per-protocol analyses. Hypotheses will be tested using mixed analysis of variance (ANOVA) for each intervention separately, with time (baseline, post-intervention) as the within-group variable and intervention arm (intervention, wait-list) as the between-group variable. Post-intervention between-group effect sizes (Cohen’s *d*) and 95% confidence intervals will be reported. Interaction effects will be followed up with within-group *t* tests, with Cohen’s *d* effect sizes and accompanying 95% confidence intervals for within-group change.

Qualitative data will be transcribed and thematic analysis will be performed in accordance with the Braun and Clarke [7] protocol. This will involve the researcher leading on the qualitative aspect of the study reading and re-reading transcripts, allocating codes to single units of meaning within each transcript, identifying sub-themes representing lower-order categories of meaning across participants (within CBT/MBCT-L separately) and finally identifying higher-order themes and the relationship between themes and sub-themes (for CBT/MBCT-L separately). This will be conducted under supervision from the lead author. Credibility will be checked through supervision and will be indicated through providing comprehensive extracts from participants to illustrate each theme and sub-theme.

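### The planned mixed ANOVA tests change scores, while the sample size and the reported Cohen's d use the unadjusted post-intervention difference; baseline-adjusted regression would align the two and be more precise

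*Protocol article*

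**What the plan says.** **The test** (Planned data analysis). "Hypotheses will be tested using mixed analysis of variance (ANOVA) for each intervention separately". The factors are time, with two levels, and arm. The section does not name the term that decides the hypothesis, but it continues: "Interaction effects will be followed up with within-group" t tests, reported with effect sizes and confidence intervals for change within each arm. That points to the time-by-arm interaction.

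**The estimate** (same section). The between-group effect to be reported is Cohen's d at post-intervention with a 95% confidence interval. No adjustment for baseline is mentioned.

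**The sizing** (Design and sample size). The calculation is "based on an estimated medium between-group effect on post-intervention stress outcomes", with d = 0.50, and is made "with 90% power and *p* = .05". The target is 140 completers per trial with 1:1 allocation, so 70 per arm.

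The Measures section has the questionnaire outcomes, including stress, collected at both baseline and post-intervention. No correlation between the two is given.

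**The concern.** The protocol fixes the test, the estimate and the sizing basis, and the first does not match the other two. The trial was sized for a comparison of post-intervention scores and will report an effect size on those scores, but the p-value will come from a comparison of changes.

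Two things follow. First, the power of the planned test is not the power that was calculated: it may be lower or higher, depending on a correlation that the protocol does not state. Second, the p-value and the d treat a chance baseline difference differently. One subtracts it in full and the other ignores it, so a paper could show a significant interaction beside a d whose interval includes zero, or the reverse. A single analysis, adjusting the post-intervention score for baseline, avoids both problems and uses data already planned.

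**Working it through.** **Inputs.** From Design and sample size: d = 0.50 on post-intervention stress, 90% power, p = .05 (sidedness not stated), 140 completers, 1:1. The baseline-to-post correlation r is not in the protocol; 0.3 to 0.8 is an assumed range. Equal SDs at the two times are also assumed.

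**1. The plan's own figure.** A two-sample t test on post-intervention means with d = 0.50, 90% power and one-sided 5% needs 70 per arm, or 140, which reproduces the target (actual power 90.3%). Two-sided 5% needs 86 per arm, or 172; at 140 the two-sided power is 83.6%. Then 140/0.60 = 233.3, rounded up to 234, which also reproduces. So the sizing is for a post-score comparison. Because sidedness is open, both bases are shown below.

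**2. What the interaction tests.** With two time points, the interaction F equals the squared t statistic for the difference between arms in mean change. A direct computation on one simulated data set gave 8.438 for both.

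**3. Variances relative to the post-only comparison.**
- Change score: 2(1 − r).
- ANCOVA (post-intervention score adjusted for baseline): 1 − r².
- Ratio of ANCOVA to change score: (1 + r)/2, which is below 1 for every r below 1. It is 0.65 at r = 0.3, 0.75 at 0.5 and 0.85 at 0.7.

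The change score has more variance than post-only when 2(1 − r) > 1, that is when r < 0.5, and less when r > 0.5.

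**4. Power at 70 per arm.** The effective effect size is 0.50/√(variance factor), and the noncentrality is that value × √(70/2). At r = 0.3 the effective sizes are 0.50/√1.4 = 0.423 (change score) and 0.50/√0.91 = 0.524 (ANCOVA). For comparison, post-only power is 83.6% two-sided and 90.3% one-sided at every r.

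| Assumed r | Two-sided: change / ANCOVA | One-sided: change / ANCOVA | Completers for two-sided 90%: change / ANCOVA |
|---|---|---|---|
| 0.3 | 69.9% / 86.8% | 80.0% / 92.5% | 238 / 156 |
| 0.4 | 76.5% / 89.3% | 85.1% / 94.1% | 204 / 144 |
| 0.5 | 83.6% / 92.4% | 90.3% / 96.0% | 172 / 130 |
| 0.6 | 90.7% / 95.7% | 95.0% / 97.9% | 138 / 110 |
| 0.7 | 96.7% / 98.4% | 98.4% / 99.3% | 104 / 88 |
| 0.8 | 99.6% / 99.8% | 99.9% / 99.9% | 70 / 64 |

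A simulation of 8,000 trials each at r = 0.3, 0.5 and 0.7 gave two-sided powers of 69.2/86.8, 83.4/92.1 and 96.8/98.4%. All three estimators (change, post-only, ANCOVA) centred on the true difference of −0.50.

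**5. How test and estimate can part.** Write B for the difference between arms at baseline and P for the difference at post-intervention, in SD units. The reported d estimates P, the interaction tests P − B, and ANCOVA estimates about P − rB. Randomisation makes B zero on average, but its standard error at 70 per arm is √(2/70) = 0.169 SD. A one-standard-error imbalance therefore separates the tested contrast from the reported one by 0.169/0.50, about a third of the assumed effect.

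**6. Finite-sample check.** Estimating the slope inflates the ANCOVA variance by about 1 + 1/(140 − 4) = 137/136. It then exceeds the change-score variance only if (1 + r)/2 > 136/137, that is r above about 0.985.

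**The case against.** The case for leaving the plan as it is has real substance.

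- **The planned test is valid.** Under randomisation it is unbiased, and it has the same expectation as the adjusted difference. This stands. A reader might infer that the p-value and the d answer different questions; they do not. They are two estimators of one effect that can differ in a given sample. How often they would lead to conflicting conclusions has not been worked out.
- **The hypothesis is worded as reducing stress**, which suits a test of change as well as a post-score comparison. This stands too, so the mismatch claimed here is only with the sample-size basis and the reported d.
- **The loss depends on an unstated r.** Above 0.5 the planned test is stronger than the one used for sizing, and by r = 0.7 to 0.8 it is nearly level with ANCOVA. This is correct, and is why the table runs to 0.8.
- **The lowest powers partly reflect sidedness.** On the one-sided basis that reproduces 140, the planned test reaches 90% from r = 0.5 upward. It would be wrong to read the 70% figure as the cost of the test choice alone.
- **The within-group t tests are not said to establish effectiveness.** A reader might infer that they will be used so, since within-arm change also contains natural change and regression to the mean. The protocol uses them only to follow up an interaction and to describe change, so that charge is not supported.
- **The decisive ANOVA term is inferred.** This is true, but the alternative does not help the plan. The arm main effect averages in the baseline, and its two-sided power, from 0.25/√((1 + r)/2), is about 45%, 40% and 36% at r = 0.3, 0.5 and 0.7.

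None of this gives a reason to prefer the change score. At every correlation considered, ANCOVA does at least as well.

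**Conclusion.** The point holds as one of precision and alignment, not of bias or invalidity. The trial is sized and reported on the unadjusted post-intervention difference but tested on change.

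The planned test is weaker than the sizing test if r is below 0.5 and stronger if it is above. ANCOVA is at least as precise throughout, apart from a negligible loss at r very near 1. Its two-sided gain at 70 per arm falls from about 17 percentage points at r = 0.3 (86.8 − 69.9) to about 9 at 0.5 and under 2 at 0.7. One-sided, the gains are about 12, 6 and 1 points.

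These figures rest on assumed correlations, equal SDs, the protocol's d of 0.50 and 70 completers per arm. They also rest on reading the interaction as the hypothesis test. The protocol does not show that the trial is underpowered because of this choice; that depends on r and on the undeclared sidedness, which is a separate matter.

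**What to change.** In Planned data analysis, replace the mixed ANOVA as the primary test with a linear regression, in each trial separately, of post-intervention DASS-21 stress on arm and baseline DASS-21 stress. From that same model, report the adjusted mean difference and a standardised effect, each with a 95% confidence interval, so that the p-value and the estimate cannot diverge. Standardise by an outcome SD named in advance, not the residual SD, so that the result stays comparable with the d of 0.50 used for sizing.

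Use the same form for the other continuous outcomes measured at baseline. Present change within each arm descriptively, without p-values.

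The cost is analysis wording only: baseline scores are already collected, and no extra participants or assessments are needed. Recruitment was still open when the article was submitted, so the change could be specified before analysis. Adjustment for Trust, clustering by group and imputation of missing data are not part of this point.

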**Methods/design:**

This protocol is for two randomised controlled trials with participant preference between the two trials and 1:1 allocation to intervention or wait-list within the preferred choice. The first trial is examining a one-day CBT stress-management workshop and the second trial an 8-session Mindfulness-Based Cognitive Therapy for Life (MBCT-L) course, with both trials comparing intervention to wait-list. The primary outcome for both trials is stress post-intervention with secondary outcomes being sickness absence, compassion for others, depression symptoms, anxiety symptoms, wellbeing, work-related burnout, self-compassion, presenteeism, and mindfulness (MBCT-L only). Both trials aim to recruit 234 staff working in the National Health Service in the UK.

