This protocol is for two RCTs examining the effectiveness of two interventions for staff working in the NHS: (1) MBCT-L and (2) CBT-based stress management. Staff will select one of these two interventions and then will be randomly assigned to either the intervention arm or to the wait-list arm within their preferred choice. Our intention in offering staff a choice between these two interventions is to increase accessibility and choice, acknowledging that no one intervention is likely to meet the needs of all staff.

Given the existing evidence for these interventions is predominantly in stress-reduction, the primary hypothesis is that both interventions will be more effective than the wait-list at reducing stress post-intervention. Secondary hypotheses are that both interventions will be more effective than the wait-list post-intervention in: (1) reducing sickness absence; (2) improving compassion for others; (3) reducing anxiety symptoms; (4) reducing depression symptoms; (5) reducing work-related burnout; (6) improving compassion for self; (7) improving wellbeing; (8) reducing presenteeism and (9) improving mindfulness (in MBCT-L participants only). We also plan to explore participants’ experiences of their chosen intervention using thematic analysis of semi-structured interviews.

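### The primary test is a change-score comparison, while the outcome and sample size concern post-intervention stress; adjusting for baseline is more precise but does not guarantee the stated 90% power

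*Protocol article*

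**What the plan says.** All references are to the protocol article.

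- **Outcome and hypothesis.** The abstract (Methods/design) says: "The primary outcome for both trials is stress post-intervention". The Background gives the primary hypothesis as "both interventions will be more effective than the wait-list at reducing stress post-intervention".
- **Sample size** (Design and sample size). "Sample size calculations are based on an estimated medium between-group effect on post-intervention stress outcomes", with d = 0.50, "90% power and *p* = .05". Whether the test is one- or two-sided is not stated. The target is given as: "The study aims to have 140 participants giving complete data sets at baseline and post-intervention within each part of the study". Allowing for 40% loss, this becomes 234 recruited per trial.
- **Test** (Planned data analysis). "Hypotheses will be tested using mixed analysis of variance (ANOVA) for each intervention separately, with time (baseline, post-intervention) as the within-group variable", and arm as the between-group variable. Interactions are then followed up with within-group t tests. The section also promises a post-intervention between-group Cohen's d with a 95% confidence interval. It names no baseline covariate.

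No baseline-to-post correlation is given anywhere in the article.

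**The concern.** The hypothesis, the sample size and the reported effect size all concern the difference in stress after the intervention. The p-value that decides the hypothesis comes from a different estimator, the difference in change. After a chance imbalance at baseline the two can disagree, and a reader would then have a post-score effect size beside a test that does not correspond to it.

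The power of the change-score test also depends on a correlation that the sample-size section never mentions, so the planned test is not the one that was sized. Baseline stress is collected from every participant before randomisation, so a more precise analysis of the same treatment effect is already available. The protocol does not use it.

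**Working it through.** **Inputs from the protocol article.** d = 0.50 on post scores, 90% power, p = .05, 140 completers per trial, 1:1 allocation (so 70 per arm), 40% loss. **Assumed.** r, because the article gives none; equal SDs at both times; complete cases; no clustering by course or workshop group.

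**1. Reproduce the plan's figure.** Two-sample t test on post scores, noncentral t, noncentrality d × √(n/2) = 0.50 × √35 = 2.96.

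- One-sided 5%: 70 per arm are needed, 140 in total, with power 90.3%. This reproduces the plan.
- Two-sided 5%: 86 per arm are needed, 172 in total. With 70 per arm, power is 83.6%.
- Loss: 140/(1 − 0.4) = 233.3, so 234. This reproduces the plan. The two-sided equivalent is 172/0.6 = 286.7, so 287.

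The 140 is therefore a one-sided figure for a post-score comparison. The interaction F test is two-sided.

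**2. What the planned test is.** With two levels of time, the interaction contrast is (post − baseline) in one arm minus the same in the other. Its F statistic is the square of the two-sample t statistic on change. Relative to the post-score variance:

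- change score: 2(1 − r)
- ANCOVA: 1 − r²
- ratio of change to ANCOVA: 2(1 − r)/(1 − r²) = 2/(1 + r), above 1 for every r < 1
- change against post score: 2(1 − r) exceeds 1 when r < 0.5

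**3. Power with 70 per arm, two-sided 5%.** Effective d is 0.5/√(2(1 − r)) for change (138 df) and 0.5/√(1 − r²) for ANCOVA (137 df). The post-score test has 83.6% throughout.

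| r (assumed) | d, change | Power, interaction | d, ANCOVA | Power, ANCOVA | Variance ratio |
|---|---|---|---|---|---|
| 0.3 | 0.423 | 69.9% | 0.524 | 86.8% | 1.54 |
| 0.4 | 0.456 | 76.5% | 0.546 | 89.3% | 1.43 |
| 0.5 | 0.500 | 83.6% | 0.577 | 92.4% | 1.33 |
| 0.6 | 0.559 | 90.7% | 0.625 | 95.7% | 1.25 |

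**4. Where each test reaches 90% two-sided.** ANCOVA at r of about 0.42; the interaction test at r of about 0.59.

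**5. Completers needed for 90% two-sided.** Interaction: 238, 204, 172 and 138 for r = 0.3, 0.4, 0.5 and 0.6. ANCOVA: 156, 144, 130 and 110.

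**The case against.** The strongest reply is that the mixed ANOVA is a valid, unbiased test under randomisation, so this is a matter of efficiency and not an error of inference. That stands. Four further points narrow the concern.

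- **ANCOVA does not restore 90%.** A reader might infer that baseline adjustment brings back the stated power. The article does not support this. It gives no r, and ANCOVA falls short of 90% two-sided below r of about 0.42. Two-sided, the 90% was not there to lose, since 140 completers give 83.6% on the comparison used for sizing. At r = 0.5 the interaction test has the same 83.6%, so at that value the whole gap from 90% comes from sidedness.
- **A low correlation is not documented.** Stress is rated over the past week, and Time 1 follows an 8-week course or comes one month after a workshop. A low r is therefore possible, but nothing in the article fixes it. Above r = 0.5 the planned test is stronger than the one used for sizing. Only the comparison with ANCOVA holds at every r.
- **The promised interval is for post scores, not change.** For that interval the variance ratio against ANCOVA is 1/(1 − r²), which is 1.10 at r = 0.3 and 1.19 at r = 0.4. The gain in the reported interval at low r is therefore smaller than the gain in the test. The article does report the effect it was sized on, but the test and the interval still come from different estimators.
- **The linear form does not suit every measure.** The presenteeism items are a yes/no question, a count of days, and a rating given only after a yes.

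**Conclusion.** The point holds as one of precision and consistency. The planned primary test compares change, whereas the outcome, hypothesis and sample size concern the post-intervention difference. Its variance is 1.25 to 1.54 times that of ANCOVA for r from 0.6 down to 0.3, which costs 5 to 17 percentage points of power at 140 completers. It falls below the post-score comparison only if r < 0.5.

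This does not show that the mixed ANOVA is biased, or that ANCOVA secures 90%. The sidedness of the sample size is a separate contributor to any shortfall, and a change of model should not hide it.

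The results rest on equal SDs at both times, complete cases, an assumed r, and no allowance for clustering in MBCT-L groups of up to 15 or workshops of up to 20. Allowing for clustering would lower power for both tests. The advantage of ANCOVA is a large-sample result; the one degree of freedom it costs is negligible at 140. The change is worth making, but the plan is not invalid without it.

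**What to change.** **Planned data analysis.** Make the primary test in each trial a linear model of Time 1 DASS-21 stress on arm, with baseline DASS-21 stress as covariate. Report the adjusted difference between arms and its 95% confidence interval from that model, so that test, estimate and interval agree. Use the same form for the continuous self-report scale scores, but not for the presenteeism items. Keep the mixed ANOVA at most as a supporting analysis.

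**Design and sample size.** State whether the test is one- or two-sided, and that 140 completers give 83.6% power two-sided on post scores. Give the ANCOVA power over a stated range of assumed r, for example 86.8% at r = 0.3 to 95.7% at r = 0.6 with clustering ignored. Do not claim that 90% is assured.

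**Cost.** A sentence or two in each section. No extra data, assessments or participants are needed, because baseline stress is already collected before randomisation. The change should be recorded before outcomes are compared between arms.

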### Interventions

#### Mindfulness-based cognitive therapy for life

MBCT-L [5] is an adaptation of MBCT originally developed by Segal, Williams and Teasdale [35, 36]. MBCT was originally developed for people with a history of recurrent depression at risk of depressive relapse and integrates CBT strategies with mindfulness practice and inquiry about practice. MBCT-L was developed to be applicable to the general population across the spectrum of wellbeing and draws on the same structure and techniques as MBCT. MBCT-L is an 8-week group intervention (with a pre-course orientation session) where participants are guided in mindfulness practice and engage with a range of CBT strategies. In this study, each group will be led by one or two MBCT teachers and will consist of up to 15 participants. Each session will take 2 h and participants will be invited to complete approximately 40 min per day of mindfulness practice and other home tasks. Content in the sessions will include guided mindfulness practices, inquiry into experiences following practices, weekly homework review, and teaching/discussion of CBT skills. The teachers leading the groups will have completed MBCT teacher training and will meet MBCT teacher criteria set out by the UK Network of Mindfulness-Based Teacher Training Organisations. Teachers will have completed additional MBCT-L training. Supervision will be provided on at least three occasions per group by a teacher who meets the supervisor criteria set out by the UK Network of Mindfulness-Based Teacher Training Organisations and who has attended 2-day MBCT-L training. Intervention completion is defined as attending at least four of the eight sessions.

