#### Cognitive behavioural therapy

This 1-day (6 h) workshop will teach participants CBT approaches to managing work-related stress. The workshop is divided into three broad sections. The first part of the workshop introduces a CBT formulation of work-related stress, drawing on the transactional theory of stress [25, 26] and the CBT maintenance cycle highlighting the inter-relationships between thoughts, feelings, physical sensations and behaviours, within work (and other) contexts. Participants will have the opportunity to formulate their own work-related stress experiences within these frameworks. The second part of the workshop overviews strategies to intervene in the maintenance cycle, with a particular focus on cognitive and behavioural strategies. The third part of the workshop encourages participants to identify specific, measurable, attainable, relevant and timely (SMART) goals, drawing on learning from the workshop and making a commitment between participants to progress towards these goals. Each workshop will consist of up to 20 participants and will be facilitated by two mental health practitioners, who demonstrate the following skills and experience between them: (1) a qualified CBT therapist or practitioner psychologist who works with CBT as their primary therapeutic model; (2) experience of facilitating therapeutic workshops or groups and (3) a senior grade within their NHS trust or a registered mental health professional with significant experience working in their NHS trust. All facilitators will attend a 1-day training event led by a clinical psychologist and CBT therapist who developed the workshop materials and will receive at least one telephone consultation session. Intervention completion is defined as attending the whole of the 1-day workshop.

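### The mixed ANOVA and the sample size ignore group delivery, so precision and power are overstated if outcomes correlate within intervention groups

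*Protocol article*

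**What the plan says.** Under Design and sample size, participants are randomised individually, "with 1:1 allocation to either intervention or wait-list within the preferred choice". The target rests on an "estimated medium between-group effect on post-intervention stress outcomes" of d = 0.50 "between the intervention and wait-list arms with 90% power and *p* = .05". It continues: "The study aims to have 140 participants giving complete data sets at baseline and post-intervention within each part of the study". The rise to 234 recruits is attributed to non-completion alone: "it is conservatively assumed that 40% of participants will fail to complete measures post-intervention". No ICC, design effect or number of groups appears.

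Under Interventions, the MBCT-L section says "each group will be led by one or two MBCT teachers and will consist of up to 15 participants", and the CBT section says "Each workshop will consist of up to 20 participants and will be facilitated by two mental health practitioners". Nothing describes wait-list participants as meeting in groups before the post-intervention assessment.

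Under Planned data analysis, the hypotheses are tested separately for each intervention by mixed ANOVA, "with time (baseline, post-intervention) as the within-group variable and intervention arm (intervention, wait-list) as the between-group variable". Those are the only two factors. No term for course, workshop or teacher is mentioned there or elsewhere.

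**The concern.** People who share a course or workshop also share its teachers, its peers and its particular run of events. Their outcomes may therefore be more alike than those of people in different groups. The wait-list arm has no matching structure before Time 1, so the design is partially nested: independent individuals in one arm, individuals within groups in the other.

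The protocol itself treats group and leader as relevant. The CBT workshop ends with participants making commitments to one another, and the engagement measures ask about satisfaction with the teacher or facilitators and comfort with other members.

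An ANOVA with only time and arm assumes independent participants. With any positive within-group correlation it understates the standard error of the comparison between arms. That reaches the primary outcome and the secondary outcomes tested the same way, in both trials. The follow-up within-group t tests in the intervention arm share the problem. The error runs one way, towards overprecise results and false positives.

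This is not a detail left to a later analysis plan, because the article names the test and its factors and fixes a sample size to go with them.

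**Working it through.** **Step 1. Reproduce the plan's figure.** Inputs from Design and sample size: d = 0.50, power 90%, p = .05, 1:1 allocation, 40% loss. A two-sample t test on independent participants with 70 per arm has noncentrality 0.5 × √(70/2) = 2.958. One-sided power at 0.05 is 90.3% (69 per arm gives 89.9%), so 2 × 70 = 140. Then 140 / 0.6 = 233.3, rounded up to 234. Both figures reproduce with a design effect of 1. The 40% allowance is used up by non-completion, so nothing is left over for clustering.

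The sidedness of p = .05 is not stated. Two-sided, 140 completers give 83.6% power, and 90% needs 86 per arm (172). That is a separate matter, so the power figures below use the one-sided basis that reproduces 140.

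**Step 2. Group sizes.** Allocated to intervention: 234 / 2 = 117. Fewest possible groups: 117 / 15 = 7.8, so 8 MBCT-L courses; 117 / 20 = 5.85, so 6 CBT workshops. With 70 completers in the arm and even loss, m = 70 / 8 = 8.75 and 70 / 6 = 11.67 completers per group.

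**Step 3. Formulas**, with clustering in the intervention arm only:
- Design effect in that arm: DE = 1 + (m − 1) × ICC
- True SE / assumed SE: r = √[(1 + DE) / 2]
- Two-sided type I error of the planned test: 2 × [1 − Φ(1.96 / r)]
- One-sided power of an analysis that allows for clustering: Φ(0.5 / √[(1 + DE) / 70] − 1.645)

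Example, CBT at ICC 0.05: DE = 1 + 10.67 × 0.05 = 1.533; r = √(2.533 / 2) = 1.125; type I error = 2 × [1 − Φ(1.7415)] = 8.2%; power = Φ(0.5 / 0.190 − 1.645) = Φ(0.983) = 83.7%.

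**Step 4. Results.** The ICC is an assumption; the protocol gives none.

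| Trial (m) | ICC | DE | r | Type I error | Power, one-sided |
|---|---|---|---|---|---|
| Either | 0 | 1 | 1 | 5.0% | 90.5% |
| MBCT-L (8.75) | 0.01 | 1.078 | 1.019 | 5.4% | 89.6% |
| MBCT-L (8.75) | 0.05 | 1.388 | 1.093 | 7.3% | 85.6% |
| MBCT-L (8.75) | 0.10 | 1.775 | 1.178 | 9.6% | 80.7% |
| CBT (11.67) | 0.01 | 1.107 | 1.026 | 5.6% | 89.2% |
| CBT (11.67) | 0.05 | 1.533 | 1.125 | 8.2% | 83.7% |
| CBT (11.67) | 0.10 | 2.067 | 1.238 | 11.4% | 77.2% |

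The power column is a normal approximation, which is why its first row is 90.5% and not 90.3%. Rounding m up to 9 and 12 gives power of 85.4% / 83.5% at ICC 0.05 and 80.4% / 76.8% at 0.10. With so few groups, small-sample degrees of freedom would lower power somewhat further.

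**Step 5. Smaller groups.** At ICC 0.05, 12 groups (70 / 12 = 5.83 completers each) give DE = 1.242 and type I error of about 6.4%. Five completers per group give DE = 1.20 and about 6.2%.

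**Step 6. Dependence on the baseline-post correlation.** The time-by-arm test works on change scores, whose variance is 2(1 − ρ) times that of a single score. If the group variance is 0.05 of the post-score variance, the ICC of change is 0.05 / [2(1 − ρ)]. For ρ = 0.3, 0.5 and 0.7 that is 0.036, 0.05 and 0.083. Type I error is then about 6.6% / 7.2%, 7.3% / 8.2% and 8.8% / 10.3% (MBCT-L / CBT).

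**Check by simulation** of the planned time-by-arm test (20,000 runs per setting, ρ = 0.5): at ICC 0, 4.8% and 5.0% for m = 9 and 12; at ICC 0.05, 7.3% and 8.3%; at ICC 0.10, 9.2% and 10.7%. This supports the formula.

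**The case against.** The strongest reply is that the harm is conditional and may be small. The protocol gives no ICC. At 0.01 the planned test is barely affected: 5.4% / 5.6% type I error and about one point of power. The group sizes are maxima. With four Trusts and courses at several locations and dates, more and smaller groups are plausible. Non-attenders kept in an intention-to-treat set would dilute any group effect further. All of this stands, and it is why the result is a range and not a single figure.

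A second reply concerns the null. Participants are individually randomised, so if the intervention affected nobody, a shared Trust or location would not inflate the error. That is right. The inflation applies to a null of zero average effect with real variation between groups. This is still a null worth protecting, since the conclusion is meant to extend to other courses and teachers.

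Three stronger readings are tempting, and the protocol does not support them:
- **That intervals are certainly too narrow and type I error certainly above 5%.** This needs a positive ICC, which is likely but not established by the document.
- **That the CBT trial is the worse affected.** The table shows larger figures for CBT only because equal ICCs were assumed. One six-hour workshop measured a month later could well have a lower ICC than eight weekly sessions measured at once, and the order would then reverse.
- **That clustering lowers power from the stated 90% to about 77% / 75%** (two-sided, ICC 0.05). The part of that fall from 90% to 84% comes from the sidedness question in Step 1.

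**Conclusion.** The point holds in conditional form. Both interventions are delivered in groups, and the named test and the 140 / 234 target treat all participants as independent. For any positive intervention-arm ICC, the intervals are too narrow, type I error for a zero average effect exceeds 5%, and 90% power is overstated.

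The size depends on an ICC that the protocol does not supply. At the fewest possible groups, it runs from negligible at 0.01 to roughly a doubling of the nominal 5% at 0.10. At 0.05 it is moderate: 7% to 8% type I error and a loss of about 5 to 7 points of one-sided power. The figures assume even loss across groups, equal ICCs in the two trials and, for the time-by-arm test, a baseline-post correlation near 0.5. They are approximate.

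**What to change.** Record the course or workshop identifier for every participant allocated to intervention. Replace the mixed ANOVA for each hypothesis with a partially nested mixed model: a random effect for course or workshop in the intervention arm only, with small-sample degrees of freedom (Satterthwaite or Kenward-Roger). Report the observed ICC. Restate the power at 140 completers over a stated range of ICCs and group sizes, saying whether the test is one- or two-sided.

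Enrolling more is not asked for. Holding 90% one-sided power would take about 240 to 320 recruits for MBCT-L (m = 9) and 244 to 357 for CBT (m = 12) over ICC 0.01 to 0.10, which is hard to justify on an unknown ICC.

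The cost is a change of analysis wording and one extra variable, which allocation to a course or workshop should already generate, although the protocol does not say so. Randomisation, interventions and measures are unchanged. The downsides are somewhat wider intervals, a lower stated power, and a group variance that will be imprecisely estimated if there are only six to eight groups.
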